#### 8.1.2 Secondary study parameters/endpoints

Secondary outcome parameters are adverse events/toxicity, cumulative cisplatin dose, time to recurrence, 2-year overall survival, costs, quality of life and patient's preference. The main oncological outcome parameters are time to recurrence and survival. Clinically relevant treatment related toxicity parameters, including specific toxicity that results in significant (grade 3 or 4) toxicity, treatment de-escalation or termination, will be recorded by the treating medical oncologist. Toxicity will be scored according to the Common Terminology Criteria for Adverse Events (CTCAE) guidelines, v5.0.

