### 10.2 Secondary study parameter(s)

Treatment toxicity is assessed with the Common Toxicity Criteria Adverse Events (CTCAE) v5.0 for a period of 24 months from the end of treatment. Toxicity scored as CDLT by the treating physician will be assessed, clarified if necessary, and reconfirmed separately. A severe toxic event is defined as a toxicity assessed as grade 3–5. Toxicities are classified as acute if they first appeared during or up to 3 months after treatment, and are classified as late if they persist, or first appear, more than 3 months after treatment. Multiple occurrences of events of a single toxicity type within an analysis time period are counted as a single event. Median numbers of toxicity events per patient (short-term [acute] toxicity and adverse long-term [late] effects, based on the TAME method of reporting toxicities) are compared between trial arms using t-tests. Proportions of patients affected by one or more toxicity event are compared between trial arms using Fishers exact test. Total administered cisplatin dose will also be recorded and means (or medians depending on the distribution) compared between trial arms.

Overall survival, disease-specific survival, loco-regional recurrences and time to recurrence are measured from the starting date of chemotherapy and compared between the three groups by the log-rank test with all-cause mortality in the intention-to treat population. Deaths are classified as being due to head and neck cancer or to other causes. Recurrences can be loco-regional or distant, or both. Patients who died from head and neck cancer causes as the first event are classed as recurrences. Patients on follow-up and patients lost to follow-up are censored at the last date at which they were known to be alive. Total time of follow-up per patient is two years. Hazard ratios and 95% CIs are generated with a univariate Cox proportional hazards model. The Schoenfeld residuals are tested by plotting the observed Kaplan- Meier values against the Cox predicted values. The effect of randomised treatment on outcome is also assessed after adjusting for known prognostic factors with a multivariate Cox proportional hazards model. At 3 months after treatment semi-structured interviews are conducted to obtain a better understanding of the patients' experience and preference for the treatment schemes, until saturation is reached. Semi-

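### Section 10.2 gives conflicting rules for deaths from other causes in disease-specific survival and the two recurrence endpoints

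*Protocol*

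**What the plan says.** Everything at issue stands in one paragraph of Protocol section 10.2.

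- Endpoints covered: "Overall survival, disease-specific survival, loco-regional recurrences and time to recurrence are measured from the starting date of chemotherapy".
- Comparison, in the same sentence and for all four: "compared between the three groups by the log-rank test with all-cause mortality in the intention-to treat population".
- Cause of death: "Deaths are classified as being due to head and neck cancer or to other causes".
- Deaths that count as recurrence: "Patients who died from head and neck cancer causes as the first event are classed as recurrences".
- Censoring: "Patients on follow-up and patients lost to follow-up are censored at the last date at which they were known to be alive".

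On the standing of these endpoints, section 8.1.2 says "The main oncological outcome parameters are time to recurrence and survival". Disease-specific survival is not among the secondary outcomes in section 2 or section 8.1.2. Section 10.2 nevertheless analyses it, and section 11.4 names it as a possible benefit.

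**The concern.** The all-cause phrase is attached to four endpoints but suits only one of them. Applied to disease-specific survival, it removes the feature that separates that endpoint from overall survival. Applied to the recurrence endpoints, it makes any death an event, whereas the recurrence rule admits only cancer deaths. An analyst cannot follow both.

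Setting the phrase aside does not fully settle the matter. The censoring sentence covers patients still on follow-up and patients lost to follow-up. Someone who dies of another cause without recurrence is neither, and no other sentence gives that patient a status.

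At stake are the event count and the meaning of time to recurrence, which the protocol ranks among its main oncological outcomes, and whether disease-specific survival is a separate endpoint at all. Allocation is unblinded (section 8.2), which is a further reason to fix the rule before any deaths are seen.

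**Working it through.** **Step 1: the two rules side by side.** Take a patient who dies of a cause other than head and neck cancer, with no earlier recurrence.

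| Endpoint | All-cause phrase taken literally | Cause-of-death and recurrence sentences |
|---|---|---|
| Overall survival | event | event |
| Disease-specific survival | event | not an event; censoring not stated |
| Time to recurrence | event | not an event; censoring not stated |
| Loco-regional recurrence | event | not an event; censoring not stated |

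Only overall survival is the same in both columns. In the first column, disease-specific survival has exactly the events of overall survival, and classifying deaths by cause serves no purpose in it.

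**Step 2: how many deaths could be affected.** The protocol states no event count or power for these endpoints, so there is no figure of its own to reproduce. The following is an illustration.

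Inputs from the protocol:
- 70 randomised patients, 1:1, so 35 per arm (sections 4.4 and 8.2).
- Compliance 55.7% on the three-weekly scheme and 86.3% hypothesised on the weekly scheme (section 4.4).
- 3-year overall survival 72%, falling to 52% in patients who do not complete the planned cycles (section 1).

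Assumptions: exponential survival; the 72% and 52% figures apply to compliant and non-compliant patients in both arms.

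2-year survival, S(2) = S(3)^(2/3):
- compliant: 0.72^(2/3) = 0.803
- non-compliant: 0.52^(2/3) = 0.647

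By arm:
- three-weekly: 0.557 × 0.803 + 0.443 × 0.647 = 0.734
- weekly: 0.863 × 0.803 + 0.137 × 0.647 = 0.782

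Expected deaths by 24 months: 35 × (0.266 + 0.218) = 16.9, about 17.

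If 20–40% of deaths are from other causes (assumption):
- deaths that change status: 0.20 × 16.9 = 3.4 to 0.40 × 16.9 = 6.8, about 3–7
- disease-specific survival: about 17 events on the literal reading, against 16.9 − 3.4 = 13.5 down to 16.9 − 6.8 = 10.1 on the cause-specific reading

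**Step 3: sensitivity.** If all 70 patients followed the 72% curve, deaths would be 70 × (1 − 0.803) = 13.8. If all followed the 52% curve, they would be 70 × (1 − 0.647) = 24.7. At a 20–40% share, 2.8–5.5 and 4.9–9.9 deaths respectively would change status.

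**Step 4: recurrence endpoints.** An other-cause death alters the recurrence count only if no recurrence came before it. The 3–7 is therefore an upper limit under the same assumptions. The protocol gives no expected number of recurrences, so no percentage change is offered.

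**The case against.** The strongest reply is that nobody would analyse the data on the literal reading. The sentences on cause of death follow at once, they would be pointless if every death counted everywhere, and the specific rule should govern the general phrase. That is probably what was intended. But the analyst must then disregard a stated rule for three of its four endpoints and infer the status of other-cause deaths. An ordinary log-rank or Cox analysis would by default censor such patients at death; the text does not say so. Had the protocol merely been silent, this could be left to a statistical analysis plan. It states a rule that conflicts with its neighbours, and that is what needs correcting.

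Several stronger inferences a reader might draw are not supported:

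- *That toxic deaths are removed and the more toxic schedule is favoured.* The protocol foresees fatal toxicity ("A severe toxic event is defined as a toxicity assessed as grade 3–5") and has only two death classes, so a treatment death may well be put under other causes. It does not say so, and an adjudicator could class it otherwise. Any effect on the comparison would require such deaths to differ between arms. They would still count in overall survival and as grade 5 toxicity.
- *That recurrence will be overstated by 1 minus Kaplan–Meier.* No such estimate is planned. Section 10.2 specifies log-rank tests and Cox models, and Kaplan–Meier values appear only in the proportional-hazards check.
- *That a competing-risks formulation would change the comparison between arms.* A cause-specific hazard comparison is numerically the same as censoring other-cause deaths. The gain is a defined status and correct recurrence proportions, not a different test result.
- *That treatment-related deaths must count as disease-specific events.* That is a choice of definition; censoring other-cause deaths is common.

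**Conclusion.** The concern holds as a conflict between stated rules in section 10.2, confined to disease-specific survival, time to recurrence and loco-regional recurrence. Taken at its word, the all-cause phrase makes disease-specific survival identical to overall survival; the sentences after it point the other way.

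In the illustration about 3–7 of roughly 17 deaths change status in disease-specific survival, and no more than that in the recurrence endpoints. The 17 rests on exponential survival, on figures from cited studies (the 72% and 52% do not come from patients with low muscle mass), and on the weekly arm reaching its hypothesised compliance. The 20–40% share is an assumption with no source in the protocol.

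The endpoints are secondary, and no power is stated for any of them. Overall survival, the primary compliance endpoint and the sample size are unaffected. The correction should be made because it costs very little and one of the endpoints is named as a main oncological outcome.

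**What to change.** In section 10.2:

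1. Limit all-cause mortality to overall survival.
2. Define the event for disease-specific survival as death from head and neck cancer.
3. For time to recurrence and loco-regional recurrence, keep the stated rule that a cancer death as first event counts as a recurrence.
4. For these three endpoints, treat death from another cause as a competing event: censored at death in the log-rank and Cox comparisons, with cumulative incidence used for any recurrence proportion shown.
5. State in advance which class a treatment-related death belongs to, and report such deaths by arm. Counting them as disease-specific events is optional.

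The cost is a few sentences, a recorded classification for treatment-related deaths and slightly more reporting. Standard software suffices.

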During chemoradiation, all patients will be frequently seen by their radiotherapist and oncologist. It is conform standard procedures to document toxicities and the researcher will collect data and add it to the database. Follow-up will consist of clinical examination every two months in the first year and every three months in the second year, for at least 24 months after treatment which is conform standard procedures. Low SMM patients will be asked to answer the EORTC QLQ-C30, EORTC-QLQ-H&N35, EQ-5D-5L and PCQ questionnaires before and 3, 6, 12 and 24 months after end of CRT. Normal SMM patients will be asked to answer the EORTC QLQ-C30, EORTC-QLQ-H&N35, EQ-5D-5L questionnaires before and 3, 6, 12 and 24 months after CRT. Questionnaires will initially be send by e-mail using Castor (EDC), but on patient's or treating physicians request paper questionnaires are available as well. Paper questionnaires will be transmitted to Castor EDC by the

executive researcher or (delegated by) the principal investigator. Patients' experience will be explored three months after CRT by qualitative research using semi-structured interviews. Semi-structured interviews will be analyzed by two investigators using thematic descriptive analyses. A cost-effectiveness analysis will be performed to compare three-weekly and weekly cisplatin treatment. Time interval between inclusion and end of treatment patient will be approximately two months, total time of follow-up will be 24 months after end of treatment. After follow-up, 6 months will be given for analysis and final report. The end of treatment is defined as the day of the last radiation session and is consistent for all groups.

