Terminology Criteria for Adverse Events (CTCAE) v5.0 guidelines (CTCAE), treatment to reduce toxicity and/or side effects and change of treatment strategy (e.g. switch from cisplatin to carboplatin). During follow-up, the patient is seen by the treating physician according to a standardized scheme. The investigator will collect data at 3, 6, 12 and 24 months after end of CRT, with a possible delay of maximum 6 weeks. Data consist of early and late toxicities, recurrence, residual disease, lost-to-follow-up and death.

Relevant and related early and late toxicities during and after CRT will be classified according to CTCAE v5.0 criteria with additional datacollection for toxicities concerning renal function, bone marrow dysfunctioning, hearing loss and neurotoxicity. Other adverse events not specified by CTCAE v5.0 will be described by the investigator in terms of symptoms, severeness, treatment and outcome. For each toxicity/event, date of start symptoms, date of diagnosis, treatment type, date of start and date of end of treatment will be collected. It will be stated whether the symptoms resolved, remained or improved and when this happened.

**Nephrotoxicity:** In case nephrotoxicity occurs, the eGFR, creatinine, and if available magnesium before CRT, during kidney dysfunction and at last moment of follow-up will be collected and compared as well.

**Ototoxicity:** When the treating physician suspects hearing loss in a patient, additional audiologic exam three months after CRT is recommended according to standard practice. Audiometry results and symptoms such as otitis, hearing loss and tinnitus, will be collected in the database to assess possible ototoxicity. Grading will be done using CTCAE v5.0 and the local preferred grading system.

**Neurotoxicity:** Neurologic symptoms will be assessed as either peripheral motor or sensory neuropathy. Other neurologic symptoms, possible related to HNSCC treatment, not classified as peripheral neuropathy will be described.

**Bone marrow dysfunctioning:** To assess degree of bone marrow dysfunctioning, blood cell count will be collected in the database. Grading will be done according to several CTCAE v5.0 subcategories 'White blood cell decreased', 'Neutrophil count decreased', 'Anemia' and 'low platelets'.

Extra procedures for this study are limited to questionnaires:

- Questionnaire EORTC QLQ-C305
- Questionnaire EORTC-QLQ-H&N3
- Questionnaire EQ-5D-5L

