### **8.6 Follow-up of subjects withdrawn from treatment**

Follow-up consists of (clinical) examination according to the national guidelines for at least 24 months after end of treatment. The researcher will collect data as previously described.

Follow-up data will be collected using EPR for withdrawn patients as well, when they were initially included, to prevent bias.

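### Recurrence endpoints are censored at the last date known alive instead of the last disease assessment, which slightly understates recurrence

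*Protocol*

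**What the plan says.** Protocol section 10.2 opens its time-to-event paragraph with four endpoints: "Overall survival, disease-specific survival, loco-regional recurrences and time to recurrence are measured from the starting date of chemotherapy". It next defines what counts as a recurrence, including that "Patients who died from head and neck cancer causes as the first event are classed as recurrences". The censoring rule follows directly: "Patients on follow-up and patients lost to follow-up are censored at the last date at which they were known to be alive". It is not limited to the survival endpoints, and no other section gives a separate rule for recurrence. The same paragraph adds: "Total time of follow-up per patient is two years".

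On how recurrence is found, section 3 says: "Follow-up will consist of clinical examination every two months in the first year and every three months in the second year". For withdrawn patients, section 8.6 plans clinical examination under national guidelines for at least 24 months after treatment, and adds: "Follow-up data will be collected using EPR for withdrawn patients as well". Section 8.1.2 names time to recurrence and survival as the main oncological outcomes.

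**The concern.** Knowing that a patient is alive settles the question for overall survival. It does not show that the disease has not returned; that takes an examination or imaging. A patient who has stopped head and neck examinations but is still recorded alive stays in the risk set for recurrence as event-free, and a recurrence in that period is missed unless it later causes a head and neck cancer death.

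Two things are at stake. The 2-year recurrence estimate is too low. And if one arm loses more patients from examination than the other, its recurrence is understated more, so the log-rank test and the hazard ratio move in its favour. The protocol fixes the rule itself, so this is not a detail left for a later analysis plan.

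**Working it through.** **The plan's own figures.** The protocol gives no event count, hazard ratio or power for recurrence. Its sample size concerns the compliance endpoint: 55.7% versus 86.3%, two-sided 5%, 80% power. The pooled two-proportion formula gives 34 per arm (33 stated; power at 33 is 79.6%), and 66/0.95 = 69.5, rounded up to 70. None of this depends on the censoring rule. The only planning figure used below is the 5% drop-out in section 4.4.

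**Assumptions, not document figures.** True recurrence is 30% at 24 months in both arms, with constant hazard. A share *f* of an arm stops being examined at a time uniform over 0 to 24 months but remains known alive.

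**Step 1: recurrences missed, ignoring cancer deaths.**
- Hazard: λ = −ln(0.70)/24 = 0.01486 per month.
- Mean probability that recurrence has occurred by the time examinations stop: 1 − 0.30/(24λ) = 1 − 0.30/0.3567 = 0.159.
- Missed per patient lost from examination: 0.300 − 0.159 = 0.141.
- Estimate under the current rule: 30 − 14.1*f* (in %).

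**Step 2: allow for head and neck cancer deaths counted as recurrences.** Assume 60% of missed recurrences lead to such a death, after a mean of 8 months (exponential). The probability of a missed recurrence with that death time falling within 24 months is ∫₀²⁴ (t/24) λe^(−λt) (1 − e^(−(24−t)/8)) dt = 0.080. Multiplied by 0.6, this is 0.048 recovered. The estimate becomes 30 − (14.1 − 4.8)*f* = 30 − 9.3*f*.

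| Lost from examination | Current rule, deaths ignored | Current rule, deaths counted |
|---|---|---|
| 5% | 29.3% | 29.5% |
| 15% | 27.9% | 28.6% |
| 25% | 26.5% | 27.7% |

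Simulation agrees within its error: 29.3%, 27.9% and 26.6% without those deaths, and 29.5%, 28.7% and 27.6% with them.

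**Step 3: difference between identical arms.**
- Equal 5% loss: none.
- 5% versus 15%: 14.1 × 0.10 = 1.4 points, or 9.3 × 0.10 = 0.9 with deaths counted.
- 5% versus 25%: 14.1 × 0.20 = 2.8 points, or 9.3 × 0.20 = 1.9 with deaths counted.

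On the hazard-ratio scale (arm losing more over arm losing fewer, true value 1, assumed 2-year recurrence 30% to 50%), simulation gave 1.00 at equal 5% loss and about 0.97 to 0.98 at 10% versus 5%. It gave about 0.92 at 20% versus 5% (0.94 to 0.95 with deaths counted) and about 0.89 at 30% versus 10% (about 0.93).

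**Step 4: the alternative rule.** Censoring at the last examination returns 30% when cancer deaths are left out. With those deaths still counted as recurrences, simulation gave 30.2%, 30.7% and 31.1% at 5%, 15% and 25% loss. Patients who die after the last examination contribute an event, while comparable survivors are censored earlier.

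**Step 5: precision.** At 30%, 35 patients per arm yield about 10 events (35 × 0.30 = 10.5). The 95% limits of the hazard ratio then span a factor of about exp(1.96 × √(1/10 + 1/10)) = 2.4 each way. In 8,000 simulated log-rank tests per scenario with identical arms, the current rule rejected in 4.8% to 5.6%, including at 5% versus 25% loss.

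**The case against.** The strongest reply is that patients keep being examined. Section 8.6 plans examinations for withdrawn patients as well; the electronic record is the source from which the data are collected, not a substitute for seeing the patient. Follow-up visits are standard care under section 3, so stopping cisplatin or leaving the study does not mean leaving surveillance. For anyone seen on schedule, the gap between last examination and last date known alive is at most about two to three months. This stands. It confines the problem to patients who actually stop being examined but are still recorded alive.

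A reader might infer that the rule favours one schedule, because toxicity and hence withdrawal could differ in an open-label trial. The protocol does not support that. It plans 5% drop-out overall without splitting it by arm, and nothing in it links withdrawal for toxicity to loss from examination. The unequal loss rates above are illustrations.

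It is also fair that counting head and neck cancer deaths as recurrences recovers part of the loss, that the alternative rule has a small bias of its own, and that any shift is far inside the sampling error of a secondary endpoint with 70 randomised patients. None of this makes being known alive evidence of being free of recurrence.

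**Conclusion.** The point holds as a minor one. The censoring rule in section 10.2 is right for overall and disease-specific survival and wrong for time to recurrence and loco-regional recurrence. At the planned 5% drop-out it understates 2-year recurrence by about 0.5 to 0.7 points. A comparison biased towards the arm losing more patients, by about 1 to 1.5 points at 5% versus 15% and 2 to 3 points at 5% versus 25%, depends on unequal loss from examination that the protocol neither states nor implies.

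These sizes rest on the assumed 30% recurrence and uniform stopping times; the lower figures also rest on the assumed share and timing of cancer deaths. The primary compliance endpoint and the sample size are untouched. It would be too strong to say that withdrawn patients are followed through records alone, or that recurrence time is generally counted long after the last examination.

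**What to change.** In section 10.2, keep the last date known alive for overall and disease-specific survival. For time to recurrence and loco-regional recurrence, state that patients without an event are censored at the date of their last disease assessment showing no recurrence. Report the recurrence estimates under the current rule as a sensitivity analysis.

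The cost is one sentence and one date field. Section 8.3 already provides that "The investigator will collect data at 3, 6, 12 and 24 months after end of CRT", and recurrence is among the items collected; the date of the last disease assessment can be taken from the same record. No clinical procedure changes.

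There are two drawbacks. Recurrence follow-up becomes slightly shorter. And because cancer deaths after the last examination still count as recurrences, the new rule overstates recurrence a little when many patients are lost: about 0.2 points at 5% loss and about 1 point at 25%. As the two rules err in opposite directions, showing both indicates how much the choice matters.
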